# Promoting sleep health during pregnancy for enhancing women’s health: a longitudinal randomized controlled trial combining biological, physiological and psychological measures, Maternal Outcome after THERapy for Sleep (MOTHERS)

**DOI:** 10.1186/s40359-024-01827-1

**Published:** 2024-06-10

**Keywords:** Perinatal sleep quality, Insomnia, Pregnancy, Post-partum, Emotional processes, Actigraphy, Sleep diary, Cortisol, Stress

## Abstract

**Background:**

Sleep is vital for maintaining individuals’ physical and mental health and is particularly challenged during pregnancy. More than 70% of women during the gestational period report insomnia symptoms. Sleep dysfunction in the peripartum increases the risk for a cascade of negative health outcomes during late pregnancy, birth, and postpartum. While psychological interventions are considered the first line treatment for sleep difficulties, they are still scarcely offered during pregnancy and there is a lack of longitudinal research combining psychological and physiological indices.

**Methods:**

The present protocol outlines a randomized controlled trial aimed at testing the long-term effectiveness of an automatized digitalized psychoeducational intervention for insomnia for expectant mothers complaining insomnia symptoms without comorbidity. Outcomes include physiological, hormonal, and subjective indices of maternal psychopathology, stress, and emotional processes, and sleep and wellbeing of the family system.

The trial is part of a longitudinal study evaluating expectant mothers from early pregnancy (within the 15th gestational week) to 6-months postpartum through 6 observational phases: baseline (BSL), 6- and 12-weeks from BSL (FU1-FU2), 2-to-4 weeks after delivery (FU3), and 3- and 6-months after delivery (FU4-5). We plan to recruit 38 women without sleep difficulties (Group A) and 76 women with sleep difficulties (Group B). Group B will be randomly assigned to digital psychological control intervention (B1) or experimental psychoeducational intervention targeting insomnia (B2). At 3 time points, an ecological-momentary-assessment (EMA) design will be used to collect data on sleep and emotions (diaries), sleep-wake parameters (actigraphy) and stress reactivity (salivary cortisol). We will also test the DNA methylation of genes involved in the stress response as biomarkers of prenatal poor sleep. Information on partner’s insomnia symptoms and new-borns’ sleep will be collected at each stage.

**Discussion:**

The proposed protocol aims at testing an easily accessible evidence-based psychoeducational intervention for expectant mothers to help them improving sleep, health, and wellbeing in the peripartum. The results could improve the understanding and management of sleep difficulties and peripartum depression.

**Trial registration:**

The study protocol has been registered on 22 April 2024 with ClinicalTrials.gov Protocol Registration and Results System (PRS), ID: NCT06379074. Protocol version: April 23, 2024.

**Supplementary Information:**

The online version contains supplementary material available at 10.1186/s40359-024-01827-1.

## Background

Improving maternal mental health is a worldwide health priority [1]. Nevertheless, several scientific sources highlighted the lack of empirical data which could drive clinical practice. Mental disorders are generally more prevalent in women than in men, especially considering specific sensible life periods, as peripartum [2, 3]. Nevertheless, pregnant and breastfeeding mothers are often excluded from biomedical research and almost neglected from clinical trials for safety reasons [4]. This partially explains lack of evidence-based research leading to effective preventive care for expectant mothers [4]. Peripartum psychopathology is highly prevalent and it is associated for all family’s members with negative health outcomes [5, 6]. Emotional and psychological peripartum wellbeing is protective for post-partum mental health, emotion regulation and maternal-fetal attachment, influencing not only mother-child attachment but also child’s later development and the emotional balance of the whole family [7]. Symptoms of insomnia, that peaks just in the immediate postpartum period, are linked with increased risk for psychopathology and somatic disorders [8–12]. Around 70% of women reported a low quality of sleep in the first month after delivery [12]. The National Sleep Foundation reported that up to 84% of women complain symptoms of insomnia during peripartum [13]. Insomnia during pregnancy is interpreted as a result of physical, endocrinological, and emotional changes and as risk factor for increased stress and psychophysiological negative outcomes, including difficulties with mother-infant attachment relationship [14]. A meta-analysis [15], based on 9 studies, reported significant correlations between perinatal insomnia and depressive symptoms. Despite high prevalence and association with several negative outcomes, there is lack of longitudinal studies which assess the relationship between insomnia during pregnancy, peripartum stress and psychopathology combining physiological and subjective outcomes [16, 17]. Furthermore, clinically, insomnia complaints during pregnancy remain underdiagnosed and undertreated [18]. The persistence of sleep problems during pregnancy represents a stressing condition which might have long-term consequences on child’s behaviour [19]. Indeed, stressing factors during peripartum lead to permanent changes in the fetus that might predispose the individual to disease later in life. Several studies showed the negative consequences of perinatal stress on neurogenesis, metabolism and the cardiovascular system in adult offspring [20], while only few data indicate that perinatal stress may also have consequences for adult sleep and cognitive phenotypes [21]. Maternal stress produces overexposure of the fetus to glucocorticoids which epigenetically impairs the development of the hippocampus, dampening its inhibitory role in the hormonal stress response. The exacerbation of the stress response in adult offspring leads to high levels of glucocorticoids, which are known to exert central effects on sleep and cognition [21]. Hypercortisolemia also impacts on FKBP5 (a gene encoding a glucocorticoid receptor co-chaperone) methylation in the blood and the hippocampus of human and mouse model of post-traumatic stress disorder [22–24]. Thus, maternal insomnia may contribute to triggering this cascade of events and have long-term consequences for health, including consequence on adult sleep phenotype.

Early psychological interventions are feasible and have been evidenced to fit with expectant mothers’ preference for health care, in a period of life in which psychotropic pharmacotherapy may be associated with patients and doctors’ concerns [25]. Cognitive-Behavioural Treatment for Insomnia (CBT-I) is the first-line treatment for insomnia and the most effective in the long term even when compared with the used hypnotics [26]. CBT-I targets those factors that maintain insomnia over time, such as dysregulation of sleep drive, sleep-related anxiety, and sleep-interfering behaviours [27]. Main CBT-I strategies include establishing a learned association between the bed and sleeping through stimulus control, restoring homeostatic regulation of sleep through sleep restriction, and reducing anxious sleep-related thoughts through cognitive restructuring. Preliminary evidence suggests that CBT-I is effective for curing insomnia during pregnancy and reduces depressive symptoms [28]. Although CBT-I is the first line treatment for insomnia disorder, there are barriers that limits its implementation, including the lack CBT-I providers and patients’ difficulties in accessing treatment [29]. Digital CBT-I (dCBT-I) is intended to meet the demand for CBT-I through the offering of treatment through digital technology [30]. dCBT-I reduces costs, increase scalability and has been proven to be effective [31, 32], becoming a recommended treatment for insomnia disorder [26]. Pregnant women may be met with additional barriers to CBT-I, including the need to menage prenatal health appointments and to reserve medical leave for them [33].

Though CBT-I has been proved to lead to long-lasting enhanced benefits compared to sleep pharmacotherapy in all adults [26], this difference may be even more relevant for pregnant women. Indeed, women and clinicians may be not prone to use medications during pregnancy due to possible negative outcomes [34]. All hypnotics available on the market and with an indication for insomnia belong to the category C (FDA, food and drug administration), for which risk cannot be ruled out because there are no satisfactory studies in pregnant women.

Psychological interventions guide patients in increasing stress regulatory skills, which may enhance resilience and efficacy in the whole peripartum period, leading to positive outcomes for the new parent-child relationship.

### Study aims

The present trial aims to evaluate the long-term effectiveness of digital psychoeducational module based on CBT-I for expectant mothers complaining insomnia symptoms without comorbid somatic or mental disorders on:

physiological, biological, genetical and subjective indices of maternal psychopathology (perinatal depression and anxiety), stress, and emotional processes; these will be assessed through cortisol levels, recording of the sleep-wake activity through actigraphies, sleep diaries, and online questionnaires;father’s and new-born’s sleep and perceived parental stress; these will be assessed through online questionnaires and sleep diaries.

### Hypotheses

#### Primary hypotheses

At post-treatment, participants in the intervention group, compared to control group, will show improvement in sleep health (physiological and self-reported) and in indices of stress and psychopathology (biological and self-reported), including perinatal depression (PND) and anxiety. Improvement in biological and self-reported indices of psychopathology and stress will be mediated by improvement in insomnia symptoms and sleep dimensions.

#### Secondary hypothesis

The improvement will be maintained at follow-ups.

## Methods

### Study design

Randomized controlled trial with three parallel arms (intervention, active control group, passive control group) with allocation ration 1:1 and 5 follow-up assessments following pregnant women from early pregnancy (within the 15° gestational week) to 6-months after birth. Three of the six phases of the study (Baseline, follow-up1 and follow-up5) will also include Ecological Momentary Assessment (EMA).

The protocol follows the Standard Protocol Items: Recommendations for Interventional Trials (SPIRIT) statement (see SPIRIT checklist available as Supplementary File S1).

### Participants

Women will be mainly recruited in the middle Italy area of Bologna and Rome (Italy) and study’s materials and sensitive data will be crepitated and archived in the Department of Biomedical and Neuromotor Sciences, University of Bologna (Italy). Different recruitment procedures will be used. Firstly, informative flyers will be distributed to women contacting public services for care through collaboration with the Unit of Obstetrics and Gynaecology of the S. Orsola Hospital in Bologna. Women assessed for the first ultrasound check will be invited to participate. Secondly, informative flyers will be distributed to private gynaecologists, personal contacts of the research group, and pharmacies. The flyer will contain a summary of the study, the contacts of the researchers and a QR-code to a website created for the study (www.studiomothers.it). The website will contain further detailed information on the study rationale, aim and procedure. Interested women will be given the possibility to fill a contact form in the website; they will then be asked for their e-mail or telephone number to be contacted for the first appointment with the researcher for the screening procedure (see below in “Procedure”).

Women will be continuously recruited for circa 8 months, starting May 2024, until reaching the required sample size of 150 (see power analysis below).

Inclusion criteria will be:

age ≥ 18 yrs. old;≤ 15th week of pregnancy at the time of recruitment;good knowledge of Italian language;no severe diagnosis of relevant somatic or mental disorder (ascertained with clinical interview);no smoking;no alcohol intake;no assumption of illegal drugs;BMI ranging 18–30 (i.e., not presenting obesity or underweight following international criteria; WHO).

During the trial, participants will have no restriction to their usual care (e.g., scheduled prenatal health appointments). They will be allowed to receive concomitant care for other mental health problems (not insomnia) after enrolment.

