### Sample size

To estimate required sample size for adequate power of the clinical trial, we used as primary outcome peripartum depression (PDS) at post-treatment. A study that compared scores on the Edinburgh Postnatal Depression Scale (EPDS) in 132 women divided into two groups, cognitive-behavioral therapy for insomnia (*N* = 89) or control group (*N* = 43), before, during and after pregnancy [35] was used. The software G-Power was used to estimate sample size: 114 women in total would be needed to have an effect power of at least 80%. Drop-out rates in previous studies were around 5 to 16% for post-treatment and short follow-ups [28, 33] and around 17% for 6 months follow-up [36]. We plan to recruit 150 participants, accounting for a dropout rate of 24%.

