### Screening

Following our recruitment strategy, all women at the first ultrasound check or all women expressing interest through the study’s website will be contacted for an appointment with a clinical psychologist for the screening, which will be conducted in a confidential space in a room at the Universities’ Department involved (Department of Biomedical and Neuromotor Sciences, University of Bologna; Department of Human Sciences, Guglielmo Marconi University of Rome). This space will be used for all in-person contact with the participants (detailed below). Study’s materials, including biological samples, will all be conserved labelled with pseudonymized codes (number and letters without personal information) in a secured room in the Department of Biomedical and Neuromotor Sciences, University of Bologna for the duration of the study. A member of the research team will explain study aims and procedure. All women will be asked to read and sign the informed consent before proceeding. A separate informed consent will be asked for the use of salivary samples for the analyses of cortisol level and DNA-methylation (see “Baseline” section). Screening will be evaluated through a psychological structured interview (Structured Clinical Interview for DSM-5, SCID-5 in the brief version QuickSCID-5) [37] and a specific interview about their sleep [38] by clinical psychologists ([name], [name], [name]). Information on pregnancy and socioeconomic variables will be collected. Women will be asked to share along with their consent, gynaecological medical data on their health status (e.g. information on pregnancy).

Eligible participants will be divided in two groups:*Group A*: control group of healthy pregnant women with no insomnia complaints (*N* = 38);*Group B*: pregnant women complaining of subthreshold or clinical insomnia (*N* = 76).

Insomnia categories (absence of insomnia; subthreshold insomnia; clinical insomnia) will be operationalized using the validated questionnaire ‘Insomnia Severity Index’ (ISI) [39]. ISI is a measure of insomnia severity in the 2 weeks before compilation. Participants provide answers on a five-point Likert scale on 7 items. The score is the simple sum of the answers to all the questions and can range from 0 to 28. The total score is interpreted as follows: no insomnia (0–7); subthreshold insomnia [8–14]; clinical insomnia [15–28].

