We expect that improvement in sleep health would lead to improvement in biological and self-report indices of wellbeing in the post-partum. Indeed, sleep difficulties in the peripartum increase the risk of perinatal depression (PND) and anxiety [15]. Moreover, sleep difficulties represent stressful experiences, which can alter the regulation of the stress response during pregnancy [21]. These alterations, in turn, can trigger epigenetic mechanisms and thus influence the stress regulatory systems of newborn with potential long-lasting effect on sleep regulation and psychopathology [21]. This first study will focus on women who reports no use of alcohol and smoking during pregnancy and no somatic or mental comorbidities, as these factors may influence and alter sleep. It should be noted that these same factors are associated with increased risk of PND [74]. If the present trial will have the expected results, MOTHERS could be tested in women with insomnia presenting risk factors for PND and thus more vulnerable to post-partum psychopathology.

Digital interventions are particularly suitable to pregnant women, as they break down barriers to psychological interventions, such as managing other prenatal health appointments and preserving personal time off for maternity leave [33]. There is thus a need for evidence-based psychoeducational programs which can be delivered digitally or in-person in the context of routine care of pregnant women. Sleep health is an important component, as it is routinely done with nutrition and physical activity. MOTHERS is intended to be delivered digitally but it is also adaptable as an in-person program. Moreover, women in the intervention conditions will also have the weekly opportunity, during the interventions, to have direct contact with an expert CBT-I clinician ([name]) to express difficulties with the intervention’s contents and to have personalized feedback about their specific symptomatology. This is expected to have positive effects on women with specific difficulties and to increase adherence to the intervention, as adherence to guided digital CBT (dCBT) is higher than to unguided programs [75]. Moreover, when possible guided dCBT-I is preferable, as evidence suggest its superior efficacy to unguided dCBT-I [76, 77].

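### Recruitment closes at 150 women in total, the stated group sizes sum to 114, and nothing says how the 150 divides, so 38 analysable women per randomised arm are not secured

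*Protocol article*

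**What the plan says.** - **Closing rule (Participants):** "Women will be continuously recruited for circa 8 months, starting May 2024, until reaching the required sample size of 150". No split by group is attached.
- **Origin of the total (Sample size):** "114 women in total would be needed to have an effect power of at least 80" per cent, and then "We plan to recruit 150 participants, accounting for a dropout rate of 24" per cent. Both figures are totals over all groups.
- **Dropout evidence (Sample size):** "Drop-out rates in previous studies were around 5 to 16% for post-treatment and short follow-ups", and "around 17% for 6 months follow-up".
- **Group sizes worded as recruitment (Abstract, Methods):** "We plan to recruit 38 women without sleep difficulties (Group A) and 76 women with sleep difficulties (Group B"). The Screening section repeats 38 and 76, and the Randomization section gives 38 for B1 and 38 for B2.
- **What decides the group (Screening; Intervention):** the woman's Insomnia Severity Index (ISI) score at screening. A score below 8 places her in A and a score above 7 in B, the group of "pregnant women complaining of subthreshold or clinical insomnia". Women at the first ultrasound check and women who respond through the website are all invited, without selection on sleep.
- **Folders (Randomization):** B1/B2 codes are generated before the study starts and placed in sealed, shuffled, numbered folders. The number of folders is not printed.

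**The concern.** Efficacy rests on B2 against B1 (Hypotheses; Expected results and discussion). Group A is not randomised, and extra women in it add nothing to that contrast. What matters is therefore how many women are randomised, and the article gives two sets of numbers that do not fit together: a recruitment total of 150 and group sizes that sum to 114.

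A team following the article could act in either of two ways. It could fill the groups to 38 and 76 and stop at 114, with no room for dropout. Or it could run to 150 and accept whatever split the volunteers' ISI scores produce. Neither route guarantees 38 analysable women in each of B1 and B2.

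**Working it through.** **1. Reproduce the plan's figure.** 114 / (1 − 0.24) = 114 / 0.76 = 150. The inflation is exact. The 114 itself cannot be rebuilt, because the article gives no effect size, standard deviation or test.

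**2. Compare the group sizes with the total.** 38 + 76 = 114, and 38 + 38 + 38 = 114. The group sizes are thus the numbers before inflation, although the Abstract words them as numbers to recruit.

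**3. Reading one: 38 and 76 are recruitment numbers.** Retained per randomised arm = 38 × 0.76 = 28.9, about 29.

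**4. Reading two: 38 and 76 are retained targets, and recruitment stops at 150.** Let p be the share of recruits with ISI 8 or above and d the dropout rate. Retained per arm = 150 × p × (1 − d) / 2. To keep 76 in Group B, p must be at least 76 / [(1 − d) × 150]:

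| Dropout | Group B needed | Share of 150 needed |
|---|---|---|
| 5% | 80 | 53% |
| 16% | 91 | 60% |
| 17% | 92 | 61% |
| 24% | 100 | 67% |

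**5. What different shares deliver at 24% dropout.** The article gives no p for this sample, so the shares are assumptions. The power column is an illustration only. It uses a standardised difference of 0.65, which is the effect that gives 80% power at 38 per arm (two-sided 5% t-test), chosen because the article states no effect.

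| Share in B | Randomised in B | Retained per arm | Retained in A | Illustrative power |
|---|---|---|---|---|
| 50% | 75 | 28.5 | 57.0 | 68% |
| 60% | 90 | 34.2 | 45.6 | 76% |
| 66.7% | 100 | 38.0 | 38.0 | 80% |
| 70% | 105 | 39.9 | 34.2 | 82% |
| 84% | 126 | 47.9 | 18.2 | 88% |

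At 24% dropout, all three groups reach 38 only at a share of two thirds. Below it the randomised arms are short, and above it Group A is short.

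**6. Apply the protocol's own dropout to each group.** 76 / 0.76 = 100 in B (50 per arm) and 38 / 0.76 = 50 in A. 100 + 50 = 150.

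**The case against.** A reader might infer that the number randomised is left entirely to the mix of volunteers, or that the trial will be underpowered. The article does not support either statement.

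- **Group sizes are stated.** Scaled to 150 in the same 1:2 ratio, 38 and 76 become 50 and 100, and exactly 38 per arm remain after 24% loss. This may be what was meant. It stands as a plausible intention, but the article does not say it, and the Abstract's wording points the other way.
- **The article's own prevalence gives no shortfall in B.** The Abstract reports insomnia symptoms in more than 70% of pregnant women. At 70%, about 40 per arm remain. That figure covers the gestational period in general and is not a share with ISI 8 or above at 11 to 15 weeks. The Discussion says that smokers, alcohol users and women with comorbidity are left out "as these factors may influence and alter sleep", which could lower the share. Flyers describing the study could draw in women with sleep complaints and raise it. The net direction is unknown.
- **The 24% exceeds every dropout rate cited.** At 16%, a 60% share leaves 90 × 0.84 / 2 = 37.8 per arm, practically the target. The two-thirds threshold therefore holds only at the protocol's own allowance.
- **Quotas and caps are often left to a full protocol.** This is fair for operational detail. It does not cover two stated numbers, 114 and 150, that both appear as the number to recruit.

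**Conclusion.** The point holds as an unreconciled conflict between a stated closing rule and stated group sizes. Followed as written, the article does not secure 38 analysable women in each randomised arm. If the group sizes are recruitment numbers, about 29 per arm remain at 24% dropout. If they are retained targets, the outcome depends on the share of recruits with ISI 8 or above, which must reach 67% at 24% dropout, or 53% to 61% at the cited 5% to 17%.

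The second shortfall is conditional: at 70% it is Group A that falls short, at about 34. The power figures show relative loss under a back-solved effect and are not the trial's planned power. All retained counts assume that women who drop out leave the analysis. The Statistical analysis section says so in one sentence, although the same paragraph also promises an intention-to-treat analysis of all randomised women.

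**What to change.** State the 150 by group: 50 in A and 100 randomised in B, 50 per arm. In Participants, close recruitment on the number randomised in Group B and cap Group A at 50. Prepare the B1/B2 folders for 100. In the Abstract, Screening and Randomization, label 38, 76 and 38/38 as analysable targets.

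This uses only the protocol's own 114, 24% and 150, and leaves the total unchanged. It costs a few sentences and a matching folder count. Some women with ISI below 8 will be declined once Group A is full, and recruitment may run past 8 months if fewer than two thirds of eligible women score 8 or above.
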